**20. Attachment_6: Second Survey**

*Please complete as much information as possible about yourself (or the one you are taking care of) in the survey below.* *All information will be treated in confidence and nothing will be linked to you.*

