**6 ELIGIBILITY CRITERIA**

The population consists of people with Type 1 or Type 2 Diabetes (or at risk) as referred by Diabetes UK through their website. Other stakeholders such as platform developer and Diabetes UK staff (i.e. dieticians) will be interviewed for implementation purposes and expert opinions.

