**6.1 Inclusion criteria**

Project participants:

- Diagnosis Type 1
- Diagnosis Type 2 or at risk for Diabetes Type 2
- Relatives taking care of people with Type 1 or Type 2 Diabetes (or at risk)
- Good understanding of written and spoken English language

Platform development staff: Good understanding and know-how of platform and current project

Diabetes UK staff: Qualified and experienced dieticians working with people having Type 1 Diabetes, Type 2 Diabetes or those who are at risk for developing Type 2 Diabetes.

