**6.2 Exclusion criteria**

There are no specific exclusion criteria formulated for the current project.

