**8.5 Participant population**

Any participant who participated in the project will be subjected to statistical or thematic analyses, except for participants who withdraw from the project before data gets anonymized. This date will be explicitly mentioned in the Participant Information and will be two weeks after data collection took place. Moreover, participants who did not opt-in for their platform usage data to be shared with CU lead researchers upon referral to the platform through Diabetes UK will not be subject to statistical analyses and labelled as missing data.

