**18. Attachment_4: First Survey**

*Please complete as much information as possible about yourself (or the one you are taking care of) in the survey below.* *All information will be treated in confidence and nothing will be linked to you.*

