**Sociodemographic background**

1. What is your current age?

_________________________years old

1. What is your gender?

□ Female

□ Male

□ Other, please describe

□ Prefer not to say

1. What is your ethnicity?

□ White

□ English/Welsh/Scottish/Northern Irish/British

□ Irish

□ Gypsy or Irish Traveller

□ Any other white background, please describe ________________

□ Mixed/Multiple ethnic groups

□ White and Black Caribbean

□ White and Black African

□ White and Asian

□ Any other Mixed/Multiple ethnic background, please describe ___________

□ Asian/Asian British

□ Indian

□ Pakistani

□ Bangladeshi

□ Chinese

□ Any other Asian background, please describe ____________

□ Black/African Caribbean/Black British

□ African

□ Caribbean

□ Any other Black/African/Caribbean background, please describe

□ Other ethnic group

□ Arab

□ Any other ethnic group, please describe

□ Any other ethnic group, please describe _________________________

□ Prefer not to say

1. What is your religion?

□ No religion

□ Christian

□ Buddhist

□ Hindu

□ Jewish

□ Muslim

□ Sikh

□ Any other religion (please state_______________________________________)

□ Prefer not to say

1. What is your relationship to Diabetes?

□ Type 1 diabetes

□ Type 2 diabetes

□ Gestational diabetes

□ I have a relative with Type 1 diabetes

□ I have a relative with Type 2 diabetes

□ Other type of diabetes, please describe _________________________

□ Prefer not to say

1. What is your current employment status? (if other please specify)

□ Full-time

□ Part-time

□ Student

□ Unemployed

□ Unable to work

□ Other, please specify_________________________

□ Prefer not to say

1. What is your education level?

□ High/Secondary school

□ College

□ University - Undergraduate

□ University - Postgraduate

□ Other, please specify_________________________

□ Prefer not to say

1. What is your marital status?

□ Never married or never registered in a civil partnership

□ Married or in a civil partnership

□ Divorced

□ Separated

□ Widowed

□ Cohabiting

□ Single

□ Prefer not to say

1. How many people are currently in your household?

□ 1

□ 2

□ 3

□ 4

□ 4+

□ Prefer not to say

1. Where do you live?

□ England

□ Northern Ireland

□ Scotland

□ Wales

□ Other (please specify)

□ Prefer not to say

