**General Health Status**

We would like to know how good or bad your health is TODAY. The scale is numbered from 0 to 100. 100 means the best health you can imagine. 0 means the worst health you can imagine. Mark an X on the scale to indicate how your health is TODAY. Now, please write the number you marked on the scale in the box below.

Your health today =

[figure not shown]

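### Carers may answer about themselves or about the person they care for, and no visible survey item records which, so the before/after health change can include carers' own values and pairs that describe two different people.

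*Combined protocol and SAP*

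**What the plan says.** Section 6 describes the population without carers: "The population consists of people with Type 1 or Type 2 Diabetes (or at risk) as referred by Diabetes UK". Section 6.1 then lists, among the project participants, "Relatives taking care of people with Type 1 or Type 2 Diabetes (or at risk"). Section 6.2 removes nobody: "There are no specific exclusion criteria formulated for the current project".

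The opening instruction of the first survey (Attachment_4) asks for information "about yourself (or the one you are taking care of) in the survey below", and the second survey (Attachment_6) repeats it, again asking for answers "about yourself (or the one you are taking care of"). The items that follow are in the second person, with no carer version; the health score, for example, begins "We would like to know how good or bad your health is TODAY".

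The closest thing to a subject identifier is the relationship question under Sociodemographic background in the first survey. Its options include "I have a relative with Type 1 diabetes" and the Type 2 equivalent.

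Section 7 links a participant's surveys through a unique link and response number, which belong to the respondent. Section 8.3.2 analyses health outcomes before and after platform use within the group. Section 8.5 says "Any participant who participated in the project will be subjected to statistical or thematic analyses", apart from withdrawals and a provision for people who did not share usage data. Section 8.6, on missing or spurious data, covers only interview recording and withdrawal.

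**The concern.** A before/after comparison means something only if both measurements belong to the same person and that person is in the target population. The surveys as written secure neither condition for carers.

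Two things can go wrong. A carer without diabetes may report their own values, which then enter the health change although they do not describe the person whose diabetes made the respondent eligible. Or a carer may answer about one person in the first survey and another in the second, so that the recorded change is partly a difference between two people.

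The results are meant to inform a business-case decision (section 1, proposed project), and this change is the plan's only comparison on health outcomes. Whose data were entered cannot be reliably recovered later, because the surveys do not hold that information. Section 7.2 also says that two weeks after collection the researchers can no longer identify a participant's data for withdrawal.

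**Working it through.** **Step 1: read every visible item for a subject identifier.**

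- First survey: the relationship question can flag a relative. It does not ask whether the respondent is a carer or whose values follow. A carer answering for the patient, as the instruction allows, could tick the patient's diabetes type and would not be visible as a carer. There is no at-risk option, although section 7.1.1 says the first part of the survey verifies that status.
- Second survey: there is no relationship, diagnosis, age or gender item, and no instruction to keep to the same person.
- Both surveys: the follow-up to height, weight and waist (myself, doctor, other) records who measured, not who was measured.
- Analysis sections 8.3.2, 8.4, 8.5 and 8.6: no rule for carers and no same-person check.

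**Step 2: size of the switching problem.** The plan has no figure to reproduce; section 8.1 gives an anticipated 200-300 and says it is not statistically derived. All inputs below are assumptions, for illustration only:

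- s = 3 kg, the SD of true within-person weight change
- f = 1% or 2.5%, the share of pairs that switch person (2 or 5 of 200)
- D = 10 kg (two adults of different size) or 40 kg (for example an adult and a child), the weight difference between the two people

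If all switches run in one direction:

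- mean shift = f × D
- SD = √(s² + f(1 − f)D²)

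| D | f | Mean shift | SD |
|---|---|---|---|
| 10 kg | 1% | 0.01 × 10 = 0.1 kg | √(9 + 0.0099 × 100) = √9.99 = 3.2 kg |
| 10 kg | 2.5% | 0.025 × 10 = 0.25 kg | √(9 + 0.024375 × 100) = √11.44 = 3.4 kg |
| 40 kg | 1% | 0.01 × 40 = 0.4 kg | √(9 + 0.0099 × 1600) = √24.84 = 5.0 kg |
| 40 kg | 2.5% | 0.025 × 40 = 1.0 kg | √(9 + 0.024375 × 1600) = √48 = 6.9 kg |

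The mean shifts are upper limits. If switches run equally both ways the mean shift is about zero, but the SD stays inflated: it is √(9 + fD²), for example √(9 + 0.025 × 1600) = 7.0 kg.

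Confidence interval width scales with the SD. It grows by a factor of 3.2/3 ≈ 1.1 in the mildest case and 6.9/3 = 2.3 in the most severe.

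**Step 3: cross-check in general terms.** Let R be the between-person SD divided by the SD of true change, and treat switched pairs as independent people with equal means. The variance of the change is then multiplied by (1 − f) + 2fR².

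- f = 1%: 1.07, 1.31 and 1.71 for R = 2, 4 and 6
- f = 2.5%: 1.18, 1.77 and 2.78 for R = 2, 4 and 6

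Dividing 200 by the factor, 200 pairs carry the information of about 187, 153 or 117 pairs at 1%, and about 170, 113 or 72 at 2.5%. The effect runs from slight to substantial, depending on R.

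**Step 4: carers reporting on themselves, without switching.** If 5% to 20% of respondents did so (assumed), 0.05 × 200 = 10 to 0.20 × 200 = 40 of 200 records would describe the wrong person. If those carers' own values did not change, the mean change among people with or at risk of diabetes would be multiplied by 0.95 to 0.80.

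**The case against.** The strongest case against is about weight, not fact. Section 2 states no hypotheses, section 8.1 calls the project exploratory, and inference is planned only where data allow, so no confirmatory test depends on this. That stands, and it lowers the severity.

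A reader might infer that section 8.5 puts every respondent into one pooled estimate. It does not say so. Sections 7.5.1 and 8.3.2 plan breakdowns by diagnosis, and the relative options would let an analyst set aside respondents who declare themselves relatives at baseline. This is only a partial remedy: 8.4 omits diagnosis from its subgroup list, and a carer who ticked the patient's diabetes type stays hidden.

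A reader might also infer that someone who both has diabetes and cares for a relative cannot say so. The relationship question shows tick boxes with no single-choice rule, so more than one tick may be possible.

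Nor do the documents support saying that large false changes will occur. The frequency and direction of switching are unknown, and the most dramatic case is the easiest to see: a 40 kg change over eight weeks is an obvious outlier, and height, asked in both surveys, would expose many adult-to-child switches. No such check is planned, however, and two adults of similar height would pass it. Distortion from children's growth is speculative, since nothing says how many carers look after children and the interval is eight weeks.

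Finally, the invitation emails and participant information are not in the text reviewed and may say for whom to answer. Even so, that would not create a recorded variable in the surveys.

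**Conclusion.** The point holds. Carers are eligible, the instruction leaves the subject of the answers open in both surveys, no visible item records the choice, and the analysis sections have no carer or same-person rule. The before/after health change can therefore mix people outside the stated population with pairs that describe two people.

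The size cannot be fixed from the documents. Under the assumed inputs (SD 3 kg, 1% to 2.5% switching), it ranges from a nearly unchanged SD of 3.2 kg with a mean shift of at most 0.1 kg, to an SD of 6.9 kg with a mean shift of at most 1.0 kg. The effect on the mean vanishes if directions balance; the loss of precision does not. The documents support saying that this can happen and would often go undetected, not that it will be common or large.

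Severity: should fix, given the exploratory design and the low cost of preventing a problem that cannot be reliably repaired afterwards.

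**What to change.** Open both surveys with an item such as: *I am answering the health questions about: myself / the person I care for.* Carry the first answer forward into the second survey, so that the respondent keeps to the same person. Ask that person's diagnosis, adding an at-risk option, and age.

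In section 8.5, state that:

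- the health-outcome change analysis is limited to records about a person with Type 1, Type 2 or at risk, with the same person at both surveys;
- carers' proxy reports about such a person are kept and flagged, with a sensitivity analysis restricted to self-reports;
- carers' answers about themselves are used for usability, satisfaction and meal planning only.

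Bring section 6 into line with 6.1 on whether carers belong to the population.

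The cost is a few extra survey items, a short addition to 8.5, and the loss of some carer records from the health analysis. Those carers remain in the rest of the evaluation.

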**General Health Status**

We would like to know how good or bad your health is TODAY. The scale is numbered from 0 to 100. 100 means the best health you can imagine. 0 means the worst health you can imagine. Mark an X on the scale to indicate how your health is TODAY. Now, please write the number you marked on the scale in the box below.

Your health today =

[figure not shown]

**Diabetes Related Health Status**

1. We would like to know your height. Would you like to answer in imperial (feet, inches) or metric (metres, centimetres) units? Please specify date DD/MM/YYYY.

□ Imperial (feet, inches)

□ Metric (metres, centimetres)

[Based on answer skip to drop down menus to select height in preferred units]

1. **How was this height measured:** (if other please specify)

□ Myself

□ Doctor

□ Other, please specify_________________________

□ Don’t know

□ Prefer not to say

1. We would like to know your weight. Would you like to answer in imperial (stones, pounds) or metric (kilograms) units? Please specify date DD/MM/YYYY.

□ Imperial (stones and pounds)

□ Metric (kilograms)

[Based on answer skip to drop down menus to select weight in preferred units]

1. **How was this weight measured:** (if other please specify)

□ Myself

□ Doctor

□ Other, please specify_________________________

□ Don’t know

□ Prefer not to say

1. We would like to know your waist size. Would you prefer to answer in imperial (inches) or metric units (centimetres)? Please specify date DD/MM/YYYY.

□ Imperial (inches)

□ Metric (centimetres)

[Based on answer skip to drop down menus to select waist size in preferred units]

[figure not shown]
Above the belly button, just below the rib cage. Bend to one side to find natural crease of your waist. Measure across at this point.

1. **How was this waist size measured:** (if other please specify)

□ Myself

□ Doctor

□ Other, please specify_________________________

□ Don’t know

□ Prefer not to say

1. What is your most recent blood glucose (sugar) level? (HbA1c mmol/mol)

□ Don’t know

□ Prefer not to say

1. What is the date of your most recent blood glucose level measurement?

DD/MM/YYYY

□ Don’t know

□ Prefer not to say

1. What is your most recent blood pressure level?

Systolic (top number) mmHg [drop down menu – 70, 80, 90, 100, 110, 120, 130, 140, 150, 160, 170, 180, 190]

Diastolic (bottom number) mmHg [drop down menu – 40, 50, 60, 70, 80, 90, 100]

□ Don’t know

□ Prefer not to say

1. What was the date of your most recent blood pressure level?

DD/MM/YY

□ Don’t know

□ Prefer not to say

1. What was your most recent HDL cholesterol level (mmol/L)?

[drop down menu]

□ Don’t know

□ Prefer not to say

1. What was your most recent TOTAL cholesterol level?

______________ mmol/L [drop down menu]

□ Don’t know

□ Prefer not to say

1. What is the date of your most recent cholesterol measurement?

DD/MM/YYYY

□ Don’t know

□ Prefer not to say

1. Do you smoke?

□ Yes

□ No

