3.2 Primary endpoint/outcome

The primary outcomes are categorized as follows: (1) Outcomes directly related to the health status and condition management of the participants (e.g. weight, BMI, HbA1c, blood pressure, waist, generic health status, smoking yes/no, confidence in diabetes management and meal planning, healthy eating) and (2) Outcomes directly related to platform intervention usage:

- Number / Duration of sessions
- Number of users / average sessions per user
- New users
- Monthly Active Users / Weekly Active Users
- Specific actions:
  - # Recipes Viewed, (any indication on favourite content)
  - # Recipe Added / Saved
  - # Meal Plans created
  - # Shopping Actions
    - Carts sent online
    - Meal plans sent to cart
    - In store shopping actions - print, email, sms, app, etc.
    - Number of items shopped / value
- Platform used - app vs web app
- GA audience metrics: Demographics, Geography,
- User Retention
- Top 20 recipes (potentially)
- The average or typical meal plan including health score (potentially)

Additionally, expectations beforehand and satisfaction afterwards will be assessed. Diabetes UK will collect data regarding their traffic on the website and the amount of referrals to the online platform.

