**8.6 Procedure(s) to account for missing or spurious data**

The semi-structured interviews and case studies will be video and audio recorded. Participants will be informed that they may withdraw any time up until the point that their data is anonymised for analysis. At this point the researchers will not be able to identify their data for withdrawal. This date will be two weeks after the semi-structured interview / case study has taken place and will be mentioned in the Participant Information.

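### The written waist instruction in both surveys can be read as asking for a width rather than a circumference; correct one sentence and add a simple check (minor)

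*Combined protocol and SAP*

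**What the plan says.** Section 3.2 gives examples of primary health outcomes that include "weight, BMI, HbA1c, blood pressure, waist, generic health status". Section 8.3.2 compares health outcomes before and after platform use within the one group and names no test. Section 8.1 anticipates 200 to 300 survey respondents and says that this number was not derived statistically.

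The waist item appears under Diabetes Related Health Status in the First Survey (Attachment_4) and again in the Second Survey (Attachment_6), with the same text:

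- The stem is "We would like to know your waist size", with a choice of inches or centimetres and a request for a date.
- A programming note says "Based on answer skip to drop down menus to select waist size in preferred units". The limits of the menu are not printed.
- A figure follows that is not reproduced in the public document.
- Directly after the figure come the site, "Above the belly button, just below the rib cage", and then "Bend to one side to find natural crease of your waist. Measure across at this point".
- The next item is "How was this waist size measured", answered by who took the measurement.

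Section 8.6 is headed "Procedure(s) to account for missing or spurious data". Its text deals only with recording of interviews and withdrawal, and it sets no range or consistency check for survey values.

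**The concern.** Measuring *across* the body at a given level gives a breadth. A waist outcome is normally a girth, and nothing in the item's text says so. The respondent is at home, with no trained measurer to correct a misreading.

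Two things can then go wrong. A respondent who gives a width at both surveys reports on the wrong scale, so a real change in girth looks smaller than it is. A respondent who gives a width at one survey and a circumference at the other adds a false change of tens of centimetres to a before-after comparison that has no control group. The surveys leave some room for such mixed pairs: each asks afresh who measured, so a doctor's value may be paired with a self-measured one, and carers may answer for the person they look after.

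**Working it through.** The documents give no SD, effect size, alpha or power for waist, so there is no planned figure to reproduce. What follows is a sensitivity calculation.

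**Inputs.** From the documents: n = 200 to 300 (section 8.1), taken as complete waist pairs, which is generous because section 8.2 expects nonresponse. Assumed: a 100 cm waist, with a cross-section between a circle and an ellipse 1.5 times as wide as it is deep.

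**1. Width for a 100 cm circumference.** With semi-axes a and b, Ramanujan's approximation to the perimeter is π[3(a+b) − √((3a+b)(a+3b))]. Setting this to 100 cm, the width 2a and the error (100 − width) are:

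| a/b | Width (cm) | Error (cm) |
| --- | --- | --- |
| 1.0 | 31.8 | 68.2 |
| 1.3 | 35.8 | 64.2 |
| 1.5 | 37.8 | 62.2 |

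**2. Width at both surveys.** If body shape is unchanged, a change in width is 0.32 to 0.38 of the change in circumference. A true change of 2 cm is recorded as 2 × 0.32 = 0.64 cm to 2 × 0.38 = 0.76 cm.

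**3. One mixed pair.** Shift in mean change = error / n.

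- n = 200: 62.2/200 = 0.31 cm to 68.2/200 = 0.34 cm.
- n = 300: 62.2/300 = 0.21 cm to 68.2/300 = 0.23 cm.

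Its contribution to the SD of change is error × √[(1/n)(1 − 1/n)]. At n = 200 this is 62.2 × 0.0705 = 4.4 cm to 68.2 × 0.0705 = 4.8 cm, and it adds to the true SD in quadrature.

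**4. Three mixed pairs in 200.** Further assumptions: error 65 cm, SD of true change 4 or 6 cm, two-sided alpha 0.05.

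- All in one direction: shift = 3 × 65/200 = 0.97 cm.
- In random directions: SD = √(4² + (3/200) × 65²) = √(16 + 63.4) = 8.9 cm, or √(36 + 63.4) = 10.0 cm. The change detectable with 80% power is (1.96 + 0.84) × SD/√200, which rises from 0.79 to 1.76 cm (SD 4) or from 1.19 to 1.97 cm (SD 6). Power for a true 1 cm change falls from 0.94 to 0.36, or from 0.65 to 0.29. For a true 2 cm change it remains 0.89, or 0.81.

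**5. Clothing size mixed with circumference.** With an assumed gap of 8 cm, three pairs in 200 shift the mean by 3 × 8/200 = 0.12 cm. Power for a 1 cm change (SD 4) moves only from 0.942 to 0.930.

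**The case against.** The strongest reply is that the words are not the whole instruction. They sit directly under a figure and read like its caption. If the figure shows a tape around the body, *across* may do no more than mark the level. A missing figure is not a fault of the plan, so it cannot be said that respondents are never shown a tape. This stands, and it is the main reason the point is minor. It does not rescue the sentence, which should agree with the figure without needing it.

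The two surveys also use identical wording, so a respondent is more likely to read it the same way twice, which makes mixed pairs less likely. That stands too, but consistent widths still shrink the change (step 2). Nothing suggests that errors would all run in one direction, and random ones mostly add noise. The drop-down may already exclude width-sized values; its limits are not printed, so this can be neither credited nor denied.

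Two stronger readings are tempting. A reader might infer that a handful of misread answers will swamp the waist result. The documents do not support that: how often it would happen is unknown, the large jump needs inconsistent reading by the same person, and power for a 2 cm change stays at 0.81 or more in step 4. A reader might also infer that the question invites trouser size. The item gives an anatomical site, asks for a date and asks who measured, and step 5 shows that a few such answers would hardly matter.

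Finally, waist is one of about ten example outcomes in an exploratory project without hypotheses, and the gap in section 8.6 affects every self-reported measure. Both are fair and limit the weight of the point.

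**Conclusion.** The point holds as a wording defect of minor severity. The written instruction for a listed primary outcome can be read literally as asking for a width, in both surveys, and section 8.6 states no check that would reveal it.

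If some respondents do report widths, consistent ones show about a third of the true change (0.32 to 0.38). Each width-circumference pair shifts the mean change by 0.31 to 0.34 cm in 200 and adds a component of 4.4 to 4.8 cm to its SD. These figures rest on an assumed 100 cm waist and an assumed body shape; the power figures also rest on assumed SDs of change and an assumed number of mixed pairs. The documents give no basis for a frequency, and the unseen figure or the menu limits may already reduce it.

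**What to change.** 1. In both surveys, replace the final sentence of the waist instruction with: *Measure all the way around your body at this point with a tape measure.*
2. Confirm that the figure shows the same thing.
3. Confirm that the drop-down covers only plausible circumferences in both units. Sections 6.1 and 6.2 set no age limit and carers may answer for someone else, so choose the lower limit with that in mind.
4. Add to section 8.6 a between-survey check fixed before the data are examined: for example, a waist pair that differs by more than 20 cm is queried or set to missing. This would catch the 62 to 68 cm errors above. It would not catch widths given at both surveys, which is why the wording and the menu range matter more.

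The cost is one sentence in each survey, a check of the figure and menu, and one sentence in the analysis plan. The downside is that a few people without a tape measure may leave the item blank. Unlabelled widths cannot be reliably repaired afterwards, so the change is best made before the first survey goes out.
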